## Abstract

**Background:**

This interview study forms part of a mixed methods process evaluation of the Survivors’ Rehabilitation Evaluation after Cancer (SURECAN) trial to understand the experiences of participants (who are living with and beyond cancer) in receiving a form of acceptance and commitment therapy, and therapists providing the intervention. SURECAN is a multi-centre, pragmatic, individual participant randomised controlled trial of an intervention based on acceptance and commitment therapy supplemented by support for return to meaningful work and/or physical activity (ACT+). This qualitative study addresses the ways in which participants believe they benefit from ACT+ (or not), and how the ACT+ intervention might best be implemented into routine National Health Service (NHS) care.

**Methods:**

The study investigates experiences of ACT+ by different participants to understand how we can optimise the ACT+ intervention and its delivery (assuming the intervention is successful). We will conduct individual interviews with participants who have taken part in the active arm of the SURECAN trial to understand their experiences of engaging with and receiving ACT+, their perceptions of the impact of the therapy, and relevant contextual factors influencing these experiences. In particular, we will focus on comparing our interview findings between those trial participants who improved and those who failed to improve (or worsened), in terms of quality of life following ACT+. Additionally, we will conduct individual interviews with therapists who have delivered ACT+ as part of the SURECAN trial, to understand their experiences of delivering ACT+.

**Conclusions:**

Consistent with other qualitative protocols, this protocol is not registered. Instead, it is shared as a means of documenting ahead of time, how we are endeavouring to understand the ways in which a newly trialled talking therapy is received by patients and therapists, and how (if successful) it might be incorporated into the NHS.

## Introduction

This interview study will form part of the mixed methods process evaluation of the Survivors’ Rehabilitation Evaluation after Cancer (SURECAN) trial, which will be conducted following Medical Research Council guidance
^
1
^. The SURECAN trial is directed to people who have completed cancer treatment with curative intent. For example, some people with prostate cancer continue with long-term, ongoing maintenance treatment in the form of androgen suppression therapy. People receiving this type of maintenance treatment are eligible for recruitment into the SURECAN trial. In addition, people with certain haematological cancers are treated with the intention of long-term remission, which means they are never technically disease-free. This is why we have included within our eligibility definition “treated with curative intent/long-term remission”. For these reasons, we prefer to use the term ‘living with and beyond’ cancer. SURECAN is a multi-centre, pragmatic, individual participant randomised controlled trial of an intervention based on acceptance and commitment therapy (a talking therapy) supplemented by support for return to meaningful work and/or physical activity, according to the preferences of the individual study participant, known as ‘ACT+’.

ACT+ is personalised to participants and includes a range of theoretically informed interventions which target people's experience of symptoms, distress and quality of life. As part of the intervention, behavioural goals are not standardized. Instead, we are interested in understanding the full range of experiences and behaviours of participants in relation to their health. We do not standardise behaviour patterns. While quantitative research aims to standardise and limit variables under investigation, qualitative research (separate from the therapy under investigation) as undertaken in this study does not pre-specify what should be attended to, as it is designed to explore complex phenomena
^
2
^.

Trial participants receive up to eight one-hour sessions of ACT+ weekly or fortnightly delivered by telephone or online. Therapists attend an ACT+ training workshop delivered over two to three days, and receive regular supervision during the trial from an experienced cognitive behavioural therapist with extensive training in ACT. We have reported in more depth on the development and evaluation of the training programme
^
3
^. Additional information about the intervention will be available in the protocol for the main quantitative trial looking at the effectiveness and cost-effectiveness of the ACT+ intervention (to be published in the public domain in due course). The ACT+ intervention in addition to usual aftercare is compared to usual aftercare only, for patients living with and beyond cancer (SURECAN Trial IRAS: 260823 Protocol v3.0 06/02/2022). Trial participants comprise individuals who have completed treatment with curative intent for one of five cancer groups (breast, lower gastrointestinal, haematological, head and neck, urological) and are experiencing low quality of life as assessed by the Functional Assessment of Cancer Therapy: General scale (FACT-G)
^
4
^.

Importantly, instead of evaluating cancer types, we are evaluating the impact of acceptance and commitment therapy (ACT), which is an empirically supported trans-diagnostic psychological therapy for wide-ranging health conditions, including varying types of cancer
^
5
^. While psychological contexts vary broadly for different cancers and patient characteristics, the focus of acceptance and commitment therapy (ACT) is to help patients better adapt to the significant challenges they face, by promoting psychological flexibility, and helping them choose what they focus on, rather than invest energy in trying to suppress or ignore difficulties. Research suggests that ACT is helpful across a range of cancer types
^
6
^, although more research is needed to identify the features of the interventions and patient characteristics that could be used to improve results. Hence, the qualitative research proposed with diverse patients and types of cancers – where we will compare those who improve and do not improve - is crucial. Trial participants are recruited through participating hospital cancer clinics, and the ACT+ intervention is delivered by trained therapists working in either participating NHS Talking Therapies services in primary care mental health services or the charity sector.

## Purpose

This interview study addresses the ways in which participants believe they benefit from ACT+ (or not), and how the ACT+ intervention might best be implemented into routine National Health Service (NHS) care. The purpose of the study is to investigate the experience of ACT+ by different participants to understand how we can optimise the ACT+ intervention and its delivery (assuming the intervention is successful). In particular, we will focus on comparing our interview findings from those trial participants who improved and from those who failed to improve (or worsened), in terms of quality of life following ACT+. Improvement will be identified as an increase of more than 6 points on the FACT-G scale. This will only be determined for individual participants at the end of the study after data lock. Participants are sampled and interviewed by researchers who are blind to their change in FACT-G score. We anticipate our sample is large enough to meaningfully compare participants who appear to have improved and not improved on these criteria. The change or not in FACT-G will then be used to interpret the analysis. We will also capture the experience of therapists who delivered the ACT+ intervention.

We will investigate experiences of ACT+, and ACT+ delivery, in two parts:

In Part A we will conduct individual interviews with participants who have taken part in the active arm of the SURECAN trial to understand their experiences of engaging with and receiving ACT+, their perceptions of the impact of the therapy, and relevant contextual factors influencing these experiences.

In Part B we will conduct individual interviews with therapists who have delivered ACT+ as part of the SURECAN trial, to understand their experiences of delivering ACT+ to people who are living with and beyond cancer.

## lImportance and theoretical framework

We will draw on Normalisation Process Theory
^
7
^, a theory that focuses on how innovations are incorporated into systems like the NHS. This approach essentially means that in our lines of questioning both participants and therapists, we will ensure to cover specific contexts of the trial; coherence (i.e. how people make sense) of the approaches used; cognitive participation (how people think about the delivery of the innovation); collective action (what people do to deliver an innovation); and reflective monitoring (how people evaluate their contributions and/or the consequences of the trial). This will ensure we ask pertinent questions of both trial participants and therapists; that we elicit narratives in order to explore how trial participants subjectively appraise their experiences related to ACT+; and explore how to best integrate ACT+ into the NHS should the therapy prove useful
^
8,
9
^. This current qualitative study is particularly important because if the SURECAN trial is successful, and ACT+ is integrated into the NHS, it is critical to know more about why some patients benefit and others do not. This is so that ACT+ can be optimised to help the greatest number of patients possible in the NHS. When we used a similar study approach in a previous trial of Graded Exercise Therapy, we discovered factors linked to participant improvement (e.g. patient motivation, being able to tolerate an initial phase of no improvement)
^
10
^. Thus, this information allows practitioners to subsequently refine their treatment approach to address factors that will improve the likelihood of success.

## Preregistration

Currently, templates for preregistering qualitative protocols are generally not yet well developed for qualitative research (e.g. quantitative assumptions, templates not fitting qualitative research paradigms), especially given qualitative research involves ongoing iterative changes to study designs to respond to emerging insights in the field
^
11
^. There is still some work needed to ensure templates are suitable for qualitative preregistration
^
12
^, and for this reason we have not preregistered our protocol.

## Research questions

Our research questions for part A are:

1)What are the differences in treatment perceptions and experiences between those trial participants who improved and those who did not following ACT+?2)Why might different kinds of participants do better than others with ACT+?3)How do participants explain the influence of life contexts on their outcomes?4)How can we optimise the ACT+ intervention and its delivery, with regard to future implementation?

Our research question for part B is:

1)How can we optimise the ACT+ intervention and its delivery, with regard to future implementation?2)Why do therapists think different kinds of participants might do better than others with ACT+?

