## Sample and recruitment for part A

### Eligibility criteria

The inclusion criteria are:

1.participant in intervention arm of trial2.received at least four sessions of ACT+ (Note: Four sessions of ACT+ were considered the minimum ‘optimal dose’, where improvements generally take at least 4 sessions for those with common mental health problems who are likely to respond to short-term psychological treatments
^
13
^.)3.no longer receiving ACT+

The exclusion criteria are:

1.did not give consent to be approached for an interview2.more than 14 months since final ACT+ session

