## Data analysis and data management

### Data analysis

Interviews will be audio-recorded and transcribed
*verbatim* by a professional transcribing service with which the university has an agreement, including to treat audio recordings and the resultant transcripts as strictly confidential. The qualitative researcher will review transcripts against the audio recordings to correct any errors and remove any identifying information.

Data will be managed in the qualitative data analysis software environment NVivo. All transcripts, once checked for accuracy and anonymised, will be uploaded to NVivo and coded. A close thematic analysis of the data will be conducted to identify ‘repeated patterns of meaning’
^
17
^. The analysis will incorporate a ‘constant comparison’ approach, to ensure that relevant data are compared with similar data systematically
^
18
^.

**
*Blinding.*
** Initially, analysis of the trial participant interview data set will be conducted using baseline data only. When the SURECAN trial has been completed and we are unblinded to the study outcomes, we will conduct further analysis, comparing interview findings from participants who improved and those who did not improve following ACT+. It will not be possible to ensure equal numbers of trial participants who improved versus those who did not. Nor will it be possible to purposively sample trial participants who improved versus those who did not, as the researchers will be blinded to treatment outcome during the sampling phase.

The data extraction to identify eligible participants will be conducted by a statistician independent to the SURECAN trial to ensure the SURECAN trial statisticians remain blind to treatment group allocation of participants.

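### A FACT-G gain of more than 6 points within the ACT+ arm shows change, not benefit from ACT+, and the plan sets no usual-aftercare figure beside it

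*Protocol article*

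**What the plan says.** Five statements in the protocol article have to be read together.

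- **Entry (Introduction).** Trial participants "are experiencing low quality of life as assessed by the Functional Assessment of Cancer Therapy: General scale (FACT-G").
- **Label (Purpose).** "Improvement will be identified as an increase of more than 6 points on the FACT-G scale". This is a raw within-person change on the scale used for entry. It is determined after data lock and then used to interpret the interviews.
- **Who is interviewed (Sample and recruitment for part A, Eligibility criteria).** The first inclusion criterion is "participant in intervention arm of trial". A further one requires at least four sessions received.
- **Contrast (Data analysis, Blinding).** The later analysis consists of "comparing interview findings from participants who improved and those who did not improve following ACT"+, all within the one arm.
- **Reading of the contrast.** The second Part A research question is "Why might different kinds of participants do better than others with ACT"+. The section on importance and theoretical framework says "it is critical to know more about why some patients benefit and others do not", so that the therapy can be optimised.

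The parent trial has a randomised comparator: "The ACT+ intervention in addition to usual aftercare is compared to usual aftercare only". The article gives that arm no part in the comparison of improved and not improved participants, and it mentions neither regression to the mean nor natural recovery.

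**The concern.** When people are selected for a low score and then graded on the change in that score, gains are expected without treatment. Part of a low entry score is a bad day, and the next measurement tends to be higher. These people have also completed cancer treatment, so some recovery over time is plausible.

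The improved group will therefore mix people helped by ACT+ with people who would have gained more than 6 points anyway. A characteristic that separates the groups may predict recovery in anyone, response to ACT+, or both. Interviews in one arm cannot tell these apart.

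This matters because the article moves from change after therapy, to benefit, to adapting the therapy. It cites an earlier trial in which factors linked to improvement were found, and says such information lets practitioners refine treatment. A factor that is only prognostic would be a poor guide for that.

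**Working it through.** **Plan's own figure.** There is none to reproduce. The article states no expected share above the 6-point cut, for either arm.

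**Inputs.** From the article: selection on low FACT-G, the cut of more than 6 points, up to 30 interviewees, and at least 9 sought in each group. Not in the article, and so assumed over a range: SD 12, 15 or 18; baseline to follow-up correlation r of 0.6, 0.7, 0.8 or 0.9; entry cut c at 0, 0.5 or 1 SD below the mean of the population being screened; natural recovery of 0, 2 or 4 points; scores normally distributed; effect of ACT+ zero throughout. This gives 3 × 4 × 3 × 3 = 108 settings.

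**Step 1: mean gain with no effect.** With φ and Φ the standard normal density and distribution function, expected gain = SD × (1 − r) × φ(c)/Φ(c). At SD 15, r = 0.7, c = −0.5: 15 × 0.3 × (0.352/0.309) ≈ 5.1 points. A simulation of 1,000,000 draws gave 5.14.

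**Step 2: share gaining more than 6 points.** Simulated with follow-up = r × baseline + noise + recovery, keeping only people at or below the entry cut.

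| Setting (zero ACT+ effect) | No recovery | +2 points | +4 points |
|---|---|---|---|
| SD 15, r 0.7, cut 0.5 SD below mean | 47% | 54% | 61% |
| SD 15, r 0.8, same cut | 39% | 47% | 56% |
| SD 15, r 0.9, same cut | 26% | 36% | 48% |
| Lowest of the grid (SD 12, r 0.9, cut at mean) | 17% | 28% | 42% |
| Highest of the grid (SD 18, r 0.6, cut 1 SD below) | 63% | 68% | 73% |

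The no-recovery column includes ordinary variation between two measurements. Without any selection, at SD 15 and r = 0.7, the share is 1 − Φ(6/(15 × √0.6)) = 1 − Φ(0.516) = 30%. Selection at 0.5 SD below the mean raises it to 47%.

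**Step 3: what this means for 30 interviewees.** With no therapy effect, the expected number labelled improved is 30 × 0.17 ≈ 5 at the low end, 30 × 0.47 ≈ 14 in the central setting and 30 × 0.63 ≈ 19 at the high end of the no-recovery range. Reaching 9 in each group would therefore not show that the groups differ in response to ACT+.

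**Step 4: how a prognostic factor can mimic response.** For a person z SD from the mean, the gain with no effect has mean −SD × (1 − r) × z and standard deviation SD × √(1 − r²). At SD 15 and r = 0.7 the latter is 15 × 0.714 = 10.7.

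- Baseline 0.5 SD below the mean: mean 2.25, P(gain > 6) = 1 − Φ((6 − 2.25)/10.7) = 36%.
- Baseline 1.5 SD below the mean: mean 6.75, P(gain > 6) = 1 − Φ((6 − 6.75)/10.7) = 53%.

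Any characteristic linked to a lower starting score would thus be more common among the improved, although ACT+ does nothing in this model.

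**The case against.** The strongest case is that the article is often more careful than the concern suggests. Its first research question, the Purpose section and the blinding paragraph speak only of change following ACT+, and the Purpose section speaks of participants who appear to have improved. The second research question is a tentative why-might question and does not itself cite the 6-point rule. The study is also about what participants believe and experience. Optimisation is conditional on the trial succeeding, so the randomised comparison decides whether ACT+ works. Life contexts are explored in the third research question and in the interview topics.

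Much of this stands. A reader might infer that the plan commits itself to reporting prognostic factors as reasons why ACT+ works. The text does not say so: the causal wording is in the second research question and in a rationale paragraph, not in an analysis rule. Three things remain. A numerical label forms the groups and is used to interpret them. A successful trial shows an average effect, not which individuals responded. And interviews can reveal outside events but not regression to the mean.

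A second tempting step is to allow talk of doing better with ACT+ only where a factor's relation to change differs by arm. That does not suit this study. Most interview topics are experiences of the therapy, such as engagement and use of the handbook, which have no counterpart under usual aftercare. It would also make exploratory qualitative findings depend on interaction tests. Analyses by arm may in any case be in the main trial protocol, which is not shown.

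**Conclusion.** The point holds as a limit on interpretation. Membership of the improved group is evidence of FACT-G change after ACT+. It is not evidence of response to ACT+, and the article's neutral and causal wordings should be brought into line.

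The size can only be given as a range under stated assumptions: about 17% to 63% above the cut with no treatment effect and no recovery, and up to about 73% with a 4-point recovery. A reader might take a narrower band, such as a third to over half, as established. The documents do not support that, because they give none of the inputs. At a correlation of 0.9 with no recovery, the share is 17% to 34%. The conclusion does not depend on where in the range the truth lies, since even the low end means about 5 of 30 interviewees.

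**What to change.** 1. In the Purpose, importance and theoretical framework, and Research questions sections, name the groups by FACT-G change after ACT+ (gain of more than 6 points, or not). State that group membership is not evidence of response to ACT+, and that factors separating the groups will be reported as associated with change.
2. After data lock, report beside the interview contrast the share of the usual-aftercare arm gaining more than 6 points at the same time point. This assumes that FACT-G is collected there at follow-up, which is likely but not stated in the article. Note that interviewees had at least four sessions, so the whole usual-aftercare arm is a benchmark and not a like-for-like control.

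The cost is a few sentences and one descriptive figure from trial data. No further interviews are needed, and sampling and blinding are unaffected. The downside is more guarded conclusions.

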## Sample and recruitment for part A

### Eligibility criteria

The inclusion criteria are:

1.participant in intervention arm of trial2.received at least four sessions of ACT+ (Note: Four sessions of ACT+ were considered the minimum ‘optimal dose’, where improvements generally take at least 4 sessions for those with common mental health problems who are likely to respond to short-term psychological treatments
^
13
^.)3.no longer receiving ACT+

The exclusion criteria are:

1.did not give consent to be approached for an interview2.more than 14 months since final ACT+ session

### Sampling

**
*Size of sample.*
** We aim to recruit up to 30 participants randomised to the intervention arm of the trial. Our previous research has shown that we need to recruit at least 9 participants in each of the improvement and non-improvement groups to make useful comparisons between participants
^
10
^. As we will not know which group the participants fall into until after the trial is unblinded, we believe that a sample of up to 30 will ensure we have sufficient numbers in each group to be able to compare patients with improved and not improved ‘quality of life’ scores.

**
*Sampling strategy.*
** We will conduct purposive sampling to obtain variation in participant characteristics. Dimensions of interest are cancer group, age, gender, and ethnic group (White, Black or Black British, Asian or Asian British, Mixed, Other), although other dimensions of interest may emerge iteratively.

### Recruitment

**
*Sample identification.*
** A list of participants eligible for this study, and their demographic characteristics, will be extracted from the SURECAN trial database. Data extraction will take place while the trial is live.

From this list of eligible participants a sample of participants will be selected to approach for interview. This sample will be selected to provide variation in participant characteristics like cancer group, age, gender, and ethnicity. Where multiple participants share the same characteristics the selections from that group will be made randomly. Once participants have been approached for interview they will be removed from any future eligible participant lists.

The process of sample selection will be iterative, with the first sample chosen to provide overall diversity but assigning more weight to selecting a variety of different ‘cancer groups’ as far as possible, the aim being to identify a group of potential participants who have been treated for different cancers. We will not aim to identify equal numbers for each cancer group as it is likely that not everyone invited into this interview study will agree to participate. The trial statistician (CR) will work closely with the qualitative researcher (SD) to determine how many trial participants need to be identified in each sampling cycle.

When interviews have been conducted with individuals recruited from the first sample selected, information regarding their cancer group, age, gender, and ethnicity (available from the extracted data and confirmed with participants at the time of interview) will be collated by the qualitative researcher to produce an overview of the variation in the sample to date. This information on the make-up of the sample will be reviewed by the research team to determine which of the categories (our dimensions of interest) should receive more weight in the second sample selection in order to increase the variation in the sample. The need for any subsequent sample selection will be determined in a similar way. The need for any subsequent data extraction/s will depend on the number of participants recruited for interview from the samples selected (as described above) in relation to our target sample size of up to 30 interviewees.

The qualitative researcher will liaise with the interview study lead (DR), the trial manager (IK), the trial statistician (CR), and the research team at regular intervals to review how the process of forming the sample is progressing and to agree the timing and objectives of any subsequent data extraction/s. See
Figure 1 (Study flow diagram) for an illustration of how participants for Part A will be identified.

